# Mesenchymal intravenous stromal cell infusions in children with recessive dystrophic epidermolysis bullosa: MissionEB protocol for a randomised, double-blinded, placebo-controlled, two-centre, crossover trial with an internal phase I dose de-escalation phase and open-label extension

**DOI:** 10.1136/bmjopen-2024-089857

**Published:** 2025-05-21

**Keywords:** DERMATOLOGY, Paediatric dermatology, Clinical Trial, Mesenchymal Stem Cells

## Abstract

**Introduction:**

Recessive dystrophic epidermolysis bullosa (RDEB) is a severe genetic mucocutaneous fragility disorder characterised by chronic blistering, slow wound healing and increased risk of squamous cell carcinoma. Current management options are very limited.

**Methods:**

This is a randomised (1:1), placebo-controlled, double-blinded crossover (A/B) trial with an internal phase I dose de-escalation (4+5 design) in the first 3 months and a 12-month continued treatment follow-on open-label study if 3-month outcome data from the crossover trial indicate safe and beneficial effects. RDEB is a rare condition, so we expect to recruit a maximum of 36 participants based on feasibility and not formal power considerations. Participants aged>6 months and <16 years will be recruited at Great Ormond Street Hospital and Birmingham Children’s Hospital. They will receive 2–3×10^6^ cells/kg intravenous infusion of umbilical cord-derived mesenchymal stem cells or placebo at the start of each crossover period (day 0) and 14 days later. The dose will be de-escalated to 1–1.5×10^6^ cells/kg depending on observed toxicity. For the main crossover trial, the primary outcome is the change in disease severity as measured by the Epidermolysis Bullosa Disease Activity and Scarring Index at 3 months from day 0 infusion. Secondary outcomes measured at 3 and 6 months from day 0 infusion include changes in general clinical appearance of skin disease, pain and itch, and quality of life. Adverse events and serious adverse events will be monitored throughout the trial.

**Ethics and dissemination:**

North East—York Research Ethics Committee approved the protocol (ref: 21/NE/0016) on 16 March 2021. Findings will be published in peer-reviewed scientific journals, presented at relevant national and international conferences, and an open-access final report submitted to the funder.

**Trial registration number:**

ISRCTN14409785. Protocol V. 8.0, 14 November 2022.

STRENGTHS AND LIMITATIONS OF THIS STUDYTo date, this is the largest cell therapy randomised trial in children with recessive dystrophic epidermolysis bullosa (RDEB).This study incorporates a placebo comparator arm to investigate the efficacy of umbilical cord-derived mesenchymal stem cell use for RDEB, improving the reliability of results.The study is double-blinded, with only the pharmacists aware of treatment allocation, eliminating response bias and the placebo effect.The study uses a mixed-methods approach, using qualitative analysis to try and collate evidence.RDEB is a rare condition, and the sample size of 36 is based on feasibility and not formal power calculations.

## Introduction

 Epidermolysis bullosa (EB) is a heterogeneous group of inherited disorders characterised by mucocutaneous fragility. Recessive dystrophic epidermolysis bullosa (RDEB) is caused by loss of function mutations in the type VII collagen gene (COL7A1), leading to reduced (RDEB intermediate) or absent (RDEB severe) type VII collagen (C7).^1^ This results in slow wound healing and can lead to fibrosis, limb contractures and an increased risk of developing squamous cell carcinoma at sites of chronic wounds and scarring.^2^ Epidemiological data on EB are variable across countries, but the latest epidemiology study from England and Wales estimated a prevalence for RDEB of 3.3 per million population and an incidence of 8.1 per million live births.^3^

Patients with RDEB experience a significant impact on quality of life and severe limitations in function and social activities. Furthermore, the humanistic and economic burden of RDEB extends beyond the patient to affect families and their interpersonal relationships.^4^

In the face of such a significant disease burden, management is currently supportive, involving a multidisciplinary team. Recent years have witnessed a collective global effort in search of effective therapies for RDEB through partnerships between academia, industry, EB charities and patients.^5^ Cell-based therapy encompasses a variety of therapies that include primary keratinocytes, fibroblasts, haematopoietic cells and mesenchymal stem/stromal cells.^6^

The fact that RDEB is considered a systemic inflammatory disease rather than a skin-limited disorder has set the basis for new investigations.^7 8^ Reported clinical trials of cell-based therapies for RDEB comprise intradermal allogeneic fibroblasts,^9 10^ bone marrow transplantation,^11^ mesenchymal stem cells (MSCs)^12^ and intravenous MSCs in children^13^,^16^ and adults with RDEB^15^,^17^ showing promising results.

The overall aim of MissionEB is to assess whether repeated infusions of umbilical cord-derived mesenchymal stem cells (UC-MSCs) are safe and can benefit children with RDEB. The primary objectives are to assess the:

Safety of third-party intravenous UC-MSCs in children with RDEB (internal phase I dose de-escalation study for safety gatekeeping).Efficacy of third-party intravenous UC-MSCs in improving disease severity in children with RDEB in the main study (crossover and open-label).

The secondary objectives for the main study are to:

Assess the safety of repeated UC-MSCs in children with RDEB.Assess the efficacy of repeated UC-MSCs in improving quality of life and symptoms (eg, pain, itch) in children with RDEB.Undertake a health economic analysis to assess the costs and consequences of treatment with UC-MSCs versus usual care.Explore patients’ and parents’ views in relation to treatment effectiveness and acceptability.

## Methods and analysis

Full detailed methods of the MissionEB trial are described in the full trial protocol, available via the trial registry (https://www.isrctn.com/ISRCTNISRCTN14409785) (online supplemental file 1).

This is a randomised (1:1), placebo-controlled, double-blinded crossover (A/B) trial with an internal phase I dose de-escalation trial in the first 3 months and a 12-month continued treatment follow-on open-label study following review of the data.

The planned overall study start date is 1 August 2020, and the overall study end date is 31 February 2027.

### Internal phase I dose de-escalation trial

An internal phase I study will be conducted on the first nine participants in Great Ormond Street Hospital (GOSH) in two cohorts (4+5 design) as displayed in figure 1. This is only for safety gatekeeping and not to find the optimal dose. Each child will undergo an initial screening, including physical examination, assessment of vital signs and disease severity assessment. Using an overall 2:1 (UC-MSCs:placebo) randomisation ratio, we will recruit four participants (each receiving the full treatment of two infusions before the next participant begins treatment) and randomise them 3:1 (UC-MSCs:placebo). Outcomes will be measured at screening, both infusion visits and then at the 3-month follow-up. Data will be reviewed by the Data Monitoring and Ethics Committee (DMEC). If toxicities, defined as suspected unexpected severe adverse reaction (SUSAR) within 48 hours of infusion, are found in one (or fewer) participant receiving the active treatment, we will proceed to confirm the safety of this dose; a further five participants will be randomised 3:2 (UC-MSCs:placebo). If no further toxicities are found, we will progress to the main two-period crossover study. Of note, dose de-escalation or expansion decisions will be based on three participants randomised to UC-MSCs in each cohort receiving at least one infusion.

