### Randomisation and blinding

During both the internal phase I dose de-escalation trial and the main crossover trial, the allocation sequence will be generated by the randomisation statistician using a validated web-based randomisation system within the Sheffield Clinical Trials Research Unit (CTRU). Site research staff blind to the treatment allocation will enter their details on the randomisation system. The randomisation email will be received by the pharmacy and the UC-MSC manufacturer (INmuneBio), who will make up the participant treatment as instructed (either placebo or active treatment) and label this with the participant identifier.

For the internal dose de-escalation trial, participants will be randomised in four cohorts and the choice of the cohort block depends on toxicity decisions made by the DMEC after each cohort (figure 1). The first nine participants are divided into two cohorts, all allocated using simple randomisation: the first four participants will be randomised (3:1) to receive (UC-MSCs:placebo) and the second five participants will be randomised (3:2) to receive (UC-MSCs:placebo). This gives an overall allocation (6:3) for these nine participants to receive (UC-MSCs:placebo). It should be noted that treatments stated here are technically for the first period of the crossover trial. These participants will only receive their second period treatments of the crossover if no concerning toxicity issues are found.

For the main crossover trial, participants will be randomised (to achieve 1:1 overall allocation) to either receive UC-MSCs (in period 1) followed by a placebo (in period 2) or placebo (in period 1) followed by UC-MSCs (in period 2) using simple blocked randomisation. Only the randomisation statistician will have access to the block size during the trial. Participants who have already received period 1 and 2 treatments on the correct UC-MSCs dose during the internal dose de-escalation trial will not be re-randomised again in the main crossover trial as they have contributed valid data for both periods. However, in the event that the dose needs to be de-escalated, participants who previously took part in the dose de-escalation study on a higher dose will washout for at least 9 months and be re-randomised to take part in the main crossover trial using the new, lower dose.

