### Intervention and placebo control

#### Internal phase I dose de-escalation trial

The investigational medicinal product (IMP) is a suspension of allogenic UC-MSCs, in a solution containing Dulbecco’s phosphate buffer saline, ZENALB (a solution of human albumin serum) and dimethyl sulfoxide. The placebo consists of the same solution, minus the allogenic UC-MSCs. The full composition of the IMP and placebo is described in Section 6.1 of the full protocol. Each participant will receive two intravenous infusions (days 0 and 14), administered as a slow bolus. At the start, participants within a cohort will receive 2–3×10^6^ cells/kg (or placebo). If dose de-escalation is triggered based on observed toxicity (figure 1), then participants in subsequent cohorts will receive 1–1.5×10^6^ cells/kg (or placebo).

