### Primary outcomes

#### Internal phase I dose de-escalation trial

Toxicity as defined by a participant experiencing a SUSAR within 48 hours of a participant receiving an infusion.

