### Statistical analysis

#### Internal dose de-escalation phase

The objective of this phase is to monitor the safety of the proposed dose based on the assessment of toxicity data that relates to all SUSARs due to study treatment as deemed by the study clinicians. These data will be assessed by the DMEC, who will recommend whether to continue with the proposed dose, halve the proposed dose to the main crossover trial or stop the trial if the proposed dose is deemed unsafe.

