#### Crossover trial

The main crossover trial will be reported according to the Consolidated Standards of Reporting Trials extension for reporting randomised crossover trials.^21^ The primary analysis will be based on the intention-to-treat principle that will include participants with outcome data on two periods of the crossover design.

The study is not formally powered, and estimation rather than formal hypothesis testing is the primary aim of the analysis, although p values may be provided when frequentist statistical models are fitted.

The primary outcome is the change in disease severity as measured by the change in EBDASI total score (across all five domains) at 3 months from day 0.^22^ This outcome will be analysed using a linear mixed-effects model that will include treatment, period and baseline (for each period, if necessary) in the model with a random effect on the participant. The difference in means (mean difference) with 95% CIs giving a range of plausible effects will be estimated using restricted maximum likelihood methods and Satterthwaite df.

To aid interpretation and ability to make probabilistic statements about the distribution of the treatment effect, an equivalent Bayesian linear mixed-effects model will be fitted using non-informative priors on model parameters. This will allow us to estimate the probabilities of the mean difference (treatment effect) being within a certain interval of potential interest to clinicians. For example, the probability of UC-MSCs causing any improvement in disease severity. The analysis of the primary outcome at 3 months and all secondary continuous outcomes will be analysed similarly. In case of missing data, the missing data mechanism will be explored, and multiple imputation may be applied as a sensitivity analysis as appropriate (where necessary).

Other sensitivity analyses will be performed to evaluate the robustness of the primary analyses. The statistical analysis plan will detail methods, including handling of endpoints measured across multiple domains.

There will be no interim analyses during the crossover trial and open-label follow-on study. However, safety data, including toxicities, will be monitored continuously by the DMEC throughout the trial.

It should be noted that judgements on the efficacy of UC-MSCs will be based on the totality of evidence from both primary and secondary clinical outcomes.

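### Phase I toxicity counts only SUSARs within 48 hours, so a serious suspected reaction classed as expected would not enter the count rule or the primary outcome

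*Protocol article*

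**What the plan says.** The Protocol article fixes phase I toxicity in three places.

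- **Methods and analysis, Internal phase I dose de-escalation trial.** The first cohort passes if "toxicities, defined as suspected unexpected severe adverse reaction (SUSAR) within 48 hours of infusion, are found in one (or fewer) participant" among those on active treatment. The second passes if there is no further toxicity. Each decision rests on three UC-MSC participants. The section describes the phase as a safety gate and not a search for the best dose.
- **Primary outcomes, Internal phase I dose de-escalation trial.** The outcome is "Toxicity as defined by a participant experiencing a SUSAR within 48 hours of a participant receiving an infusion".
- **Statistical analysis, Internal dose de-escalation phase.** The objective rests on "assessment of toxicity data that relates to all SUSARs due to study treatment as deemed by the study clinicians". No time limit is given here.

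Under Intervention and placebo control, a lower dose for later cohorts is tied to observed toxicity.

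The article also gives the DMEC a wide role. It reviews the phase I data, its toxicity decisions after each cohort determine which cohort block follows (Randomisation and blinding), and it is the body "who will recommend whether to continue with the proposed dose, halve the proposed dose to the main crossover trial or stop the trial". Under Crossover trial, "safety data, including toxicities, will be monitored continuously by the DMEC throughout the trial". AEs and SAEs are a secondary outcome that applies to phase I as well, and all adverse reactions are recorded.

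**The concern.** Expectedness is a regulatory classification. It helps decide how a reaction is reported, but it does not grade harm. A serious reaction that is already described for a cell product is no milder for the child than one that is not.

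Under the stated definition, a child with a serious suspected reaction within 48 hours that is classed as expected adds nothing to the count and is a non-event in the primary outcome. The written gate would then not respond, any response would rest on DMEC judgement, and phase I could report no toxicity although such a reaction had occurred. If the dose is kept, at most 36 − 6 = 30 children would first receive UC-MSCs after this gate. That bounds exposure, not harm.

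**Working it through.** The article gives no operating characteristics for the 4+5 rule, so there is no figure to reproduce. The check has two parts.

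**1. Definition.** The count rule and the primary outcome both require a SUSAR within 48 hours, and the analysis section relies on SUSARs. No section adds expected serious reactions, or any graded toxicity, to the count. The article spells out the first S of SUSAR as severe, but on either reading the event must be unexpected.

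**2. Illustration of size.** Inputs from the article: three UC-MSC children per cohort, at most one toxicity allowed in cohort 1 and none in cohort 2. Assumed inputs: *r*, the per-child rate of serious suspected reactions within 48 hours on UC-MSCs (2%, 5%, 10%, 20%); *u*, the share classed as unexpected (1, 0.8, 0.5); independent children; and severe read as serious. The counted rate is *q* = *u·r*.

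*Count rule alone, ignoring the DMEC.*

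P(pass) = [(1−q)³ + 3q(1−q)²] × (1−q)³

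Example with r = 10% and u = 0.8: q = 0.08, the first factor is 0.7787 + 0.2031 = 0.9818, the second is 0.7787, and the product is 0.7645.

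| r | all count (u = 1) | one fifth expected (u = 0.8) | half expected (u = 0.5) |
|---|---|---|---|
| 2% | 94% | 95% | 97% |
| 5% | 85% | 88% | 93% |
| 10% | 71% | 76% | 85% |
| 20% | 46% | 55% | 71% |

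*Primary outcome, six UC-MSC children treated.* The chance that no toxicity is recorded although at least one child had a serious suspected reaction is

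P = (1−q)⁶ − (1−r)⁶

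Example with r = 10% and u = 0.8: 0.92⁶ − 0.90⁶ = 0.6064 − 0.5314 = 0.075.

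| r | u = 1 | u = 0.8 | u = 0.5 |
|---|---|---|---|
| 2% | 0% | 2% | 6% |
| 5% | 0% | 5% | 12% |
| 10% | 0% | 7% | 20% |
| 20% | 0% | 9% | 27% |

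If no serious reaction is classed as expected (u = 1), the two definitions give the same result in both tables.

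**The case against.** **The condition is not shown to hold.** The article refers to Section 9 of the full protocol for its adverse-reaction definitions, and the decision tree is in a figure that is not shown. A reader might infer that some serious UC-MSC reaction is in fact listed as expected. Nothing in the article says so, and if none is listed the gap is empty. This stands, and it makes the size unknown. It does not alter the rule, which the article states outright and does not leave to another document.

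**The DMEC is a real safeguard.** A reader might also infer that an expected serious reaction would go unseen, or that the dose would automatically continue. The article does not support that. Such a reaction would be recorded and could be reviewed, and the DMEC may recommend halving the dose or stopping. Period 2 treatment for phase I children also depends on there being no toxicity of concern, which is broader wording than SUSAR. With three treated children per cohort, leaving room for judgement is defensible. This stands too, so the count-rule table describes the written rule and not the trial's full decision process. It does not answer the point about the primary outcome: DMEC discretion cannot change what that outcome records.

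**The rates are invented.** They are. The case with one fifth expected lies much closer to the all-counted column than the case with half expected, so both are shown.

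**Known reactions may not deserve to stop a dose.** That is a clinical judgement, and the sponsor may hold it. It would then be better to name the reactions that do not count than to let expectedness decide.

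**Conclusion.** The point holds as a badly chosen definition whose practical effect is conditional. The phase I count rule and primary outcome leave out serious suspected reactions classed as expected, and that exclusion does not follow harm. The documents do not show that any reaction would be missed in practice, or that any child would be put at risk by it.

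Under the assumed rates, with one fifth classed as expected, the written rule passes 1 to 9 percentage points more often than if every serious suspected reaction counted, and the primary outcome is silent about a serious reaction 2% to 9% of the time. With half classed as expected, the ranges are 3 to 25 points and 6% to 27%. With none, both are zero. The figures rest on assumed rates, independent children and no DMEC intervention in the count rule, and none is an estimate for this product.

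**What to change.** - **Count rule and primary outcome:** define toxicity as *any serious suspected adverse reaction to the infusion within 48 hours, whether or not expected*. This also replaces severe with serious, and the amendment should say so.
- **Statistical analysis, Internal dose de-escalation phase:** replace the reference to all SUSARs with *all serious suspected adverse reactions, expected or unexpected*. Add no 48-hour limit there, since the current text has none.
- **If phase I is already complete:** report all serious suspected reactions within 48 hours by arm beside the primary outcome, and limit any conclusion of no toxicity to unexpected reactions.

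**Cost.** These are wording changes in three sections, using adverse reactions that are already recorded. If no serious reaction is listed as expected, dropping the expectedness condition changes no count. Otherwise the gate may fire somewhat more often. With one fifth classed as expected, the count rule would fire 15% instead of 12% of the time at a 5% rate, and 29% instead of 24% at a 10% rate. With half, the changes are from 7% to 15% and from 15% to 29%. If the dose is then reduced, phase I children treated at the higher dose face at least 9 months of washout and re-randomisation.

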**Figure 1 F1:**
[figure not shown]
Internal dose de-escalation phase. DMC, data monitoring commtitee; EME, Efficacy and Mechanism Evaluation; MSCs, mesenchymal stem cells; NHS, National Health Service.

### Main crossover trial

Each child will undergo an initial screening, including physical examination, assessment of vital signs and disease severity assessment. All study participants will be randomised to receive two consecutive intravenous MSCs or placebo infusions on days 0 and 14 (figure 2). After outcome assessment at 9 months, all children will be crossed over and receive either placebo or UC-MSCs at 9 months and 14 days later. The placebo effect, if any, is expected to tail off by 3 months. In the EBSTEM trial, the maximum benefit of the UC-MSCs was seen at 3 months, and in one patient the beneficial effects lasted for up to 6 months.^14^ This was the primary reason behind the 9-month washout period.

**Figure 2 F2:**
[figure not shown]
Overview of the phase I, crossover and open-label study timelines. EBDASI, Epidermolysis Bullosa Disease Activity and Scarring Index; MSCs, mesenchymal stem cells; QoL, quality of life.

Outcomes will be measured at 0, 3, 6, 9, 12 and 15 months. All children will be followed up every 3 months as part of their clinical care for the first year following the first infusion. A cost consequence analysis will also be undertaken.

We will explore the impact of the treatment on participants by conducting interviews with children and parents (n=10 dyads or individuals) in both arms at the 3-month and 12-month follow-up timepoints.

